**Aims:**

Our primary aim is to determine whether 16 sessions of active iTBS applied to the left DLPFC results in reduced craving and opioid use, and higher treatment retention, relative to sham. In a secondary aim, we will also examine whether iTBS-related changes in craving are associated with changes in functional connectivity between the left DLPFC and both the dorsal striatum and anterior cingulate cortex.

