## Introduction

Opioid use disorder (OUD) affects over 16 million people each year and remains the leading cause of fatal overdoses worldwide [1]. Gold-standard medications for the treatment of OUD, such as buprenorphine, the most widely prescribed medication for OUD [2], safely reduce mortality and drug use [3,4]. However, even with buprenorphine treatment, relapse and treatment discontinuation rates remain high for people with OUD; the three-month period after treatment initiation presents the highest risk for return to use [5,6]. Within 6 months of starting buprenorphine, only 50% of patients will continue treatment, and 91% will return to use [7]. Together, these data highlight the need for adjunctive treatments that address the drivers of return to use and treatment discontinuation.

Noninvasive brain stimulation has been explored as a treatment for substance use disorders (SUDs), including OUD. Transcranial magnetic stimulation (TMS) is one form of noninvasive brain stimulation that uses electromagnetic pulses to modulate cortical excitability and induce neuroplastic changes [8,9]. The U.S. Food and Drug Administration (FDA) has cleared TMS for the treatment of depression, obsessive-compulsive disorder and for smoking cessation [10] with clinical protocols typically administering stimulation over the dorsolateral prefrontal cortex (DLPFC) [11]. Within these applications, intermittent theta burst stimulation (iTBS), a specific type of patterned TMS, has demonstrated significant clinical utility. iTBS is thought to increase synaptic long-term potentiation by enhancing cortical excitability [12,13]. Crucially, reviews and meta-analyses across multiple SUDs have shown that TMS (including iTBS) is effective at reducing craving and substance use [14–16]. It is hypothesized that TMS exerts therapeutic effects by targeting the neural circuits that contribute to drug craving and seeking [17].

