### Sample size

We plan to recruit up to 60 participants at each site (VUMC and SynpaticPSYCH) to obtain a completion sample of n = 50 at each site for a total of n = 100. With 80% power, a type 1 error rate of 5%, and 100 subjects across all sites, we can detect effect sizes larger than 0.40. Based on these calculations, our proposed total sample of n = 100 will provide adequate power to detect changes in craving and opioid use.

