### Randomization and blinding procedures

Randomization will be stratified by site, with independent allocation sequences generated within each site. Within each stratum, treatment assignments will be generated using a permuted block design to maintain balance between groups throughout enrollment. The study biostatistician (SV) will generate the randomization sequence. As this is a single-blind study, study personnel responsible for administering TMS will have access to the allocation sequence, maintained on a central electronic document, and will not be blinded to treatment assignment. Participants will remain blinded to the intervention they receive throughout the duration of the study. Sham (placebo) stimulation will be delivered by flipping the coil 180 degrees so that the procedure mimics the look and sound of active stimulation but deliver no stimulation to the participant. Participants will only be un-blinded if an adverse reaction to active TMS occurs and the participant can no longer remain enrolled in the study. We will make numerous attempts to retain participants in the study with phone calls, emails, and text messages.

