### Data retention and missing data

We will collect data from all participants who attend visits. If missingness in outcome or covariate values are greater than 10%, we will perform multiple imputation by chained equations using 100 resampled datasets for the primary outcome analyses and secondary analyses that do not use full image outcome variables [31,32]. We will compare results with and without multiple imputation as supplementary analyses. For full image analyses, we will use complete-case analysis. If a participant deviates from the protocol, we will perform sensitivity analyses using data collected per-protocol and including those who deviated from the protocol in separate analyses.

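### Comparing results with and without multiple imputation says little about informative dropout, because both are missing-at-random analyses

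*Protocol article*

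**What the plan says.** The section on data retention and missing data plans multiple imputation by chained equations, with 100 datasets, if more than 10% of outcome or covariate values are missing. It then adds: "We will compare results with and without multiple imputation as supplementary analyses". The other sensitivity analysis in that section is per-protocol. It deals with protocol deviations, not with what the missing values might have been. The article does not say which variables enter the imputation model.

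The primary analysis is a model for change from week 1 to week 10, adjusted for age, sex and the baseline value, fitted once for craving and once for days of use. The primary outcome section says both are also measured during the iTBS course.

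Three other statements bear on who will be missing:
- The Aims ask whether active iTBS "results in reduced craving and opioid use, and higher treatment retention, relative to sham".
- The sample size section says "We plan to recruit up to 60 participants at each site" and that the purpose is "to obtain a completion sample of n = 50 at each site for a total of n = 100".
- The Introduction reports that, within six months of starting buprenorphine, "only 50% of patients will continue treatment, and 91% will return to use".

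**The concern.** A check on missing data is useful if it can come out differently when the assumption fails. Here both analyses replace or ignore a missing week-10 value on the premise that the participant would have done as well as an attender in the same arm with the same observed values. If people who leave are doing worse than that, neither analysis sees it. If they also leave at different rates in the two arms, the treatment contrast is biased in both analyses by nearly the same amount.

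The article's own account makes this plausible. Treatment retention is expected to be better on active. The Discussion ties TMS sessions to weekly buprenorphine visits, so leaving treatment and missing study visits are likely to be linked. In the other direction, the randomization section foresees participants leaving after an adverse reaction to active TMS, while sham delivers no stimulation. A reader who sees the two analyses agree could take the craving and opioid-use results as secure against dropout when that has not been tested.

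**Working it through.** **Planned loss.** (120 − 100)/120 = 16.7%, and 100/(1 − 0.167) = 120, so the article's enrolment and completion figures fit together. This is above the 10% trigger, but the article does not say at which visit completion is counted.

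**Size of the bias.** Let p be the proportion missing in an arm, and δ the amount (in SD of craving) by which dropouts are worse than comparable attenders. Negative values favour active. Then

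effect in all randomised = effect among comparable attenders + (p_active × δ_active − p_sham × δ_sham).

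The last term is missed by both analyses when imputation uses only the analysis-model variables.

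**First simulation.** 60 per arm (1:1 assumed), baseline–outcome correlation 0.5 (assumed), effect −0.40 SD apart from dropout, 16.7% lost overall, 1,500 trials per scenario, 20 imputations, the same δ in both arms. The splits and δ are assumptions, since the article gives none.

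| Loss active / sham | δ | Formula | Full data | Attenders only | Imputed |
|---|---|---|---|---|---|
| 10% / 23.3% | 0.4 | −0.453 | −0.455 | −0.401 | −0.401 |
| 10% / 23.3% | 0.8 | −0.507 | −0.507 | −0.400 | −0.400 |
| 13.3% / 20% | 0.8 | −0.453 | −0.452 | −0.398 | −0.398 |
| 16.7% / 16.7% | 0.8 | −0.400 | −0.402 | −0.400 | −0.400 |

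In the first two rows the shared bias is 0.455 − 0.401 = 0.054 and 0.507 − 0.400 = 0.107 SD, that is 12% and 21% of the full-data effect. For 13.3%/20% the formula gives 0.4 × 0.067 = 0.027 to 0.8 × 0.067 = 0.053 SD. Reversing the arms reverses the sign.

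**Second simulation, with an on-treatment craving measure.** 120 randomised, 300 trials per scenario, 100 imputations, δ = 1 SD, effect −0.40. The last column adds an on-treatment craving measure to the imputation model, with an assumed residual correlation of 0.7 with week-10 craving.

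| Loss active / sham | Full data | Attenders only | Imputed, model variables | Imputed, plus on-treatment craving |
|---|---|---|---|---|
| 10% / 23.3% | −0.532 | −0.396 | −0.396 | −0.460 |
| 15% / 35% | −0.582 | −0.380 | −0.379 | −0.478 |
| 25% / 50% | −0.647 | −0.396 | −0.395 | −0.516 |
| 35% / 15% | −0.202 | −0.394 | −0.393 | −0.296 |

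With model variables only, the average absolute gap between the imputed and attenders-only estimates was 0.005 to 0.012 SD across all scenarios, including those with no informative dropout. With on-treatment craving the gap was 0.064, 0.098, 0.120 and 0.098 SD, against a bias of 0.136, 0.202, 0.251 and 0.192: about half each time. This is what the set-up implies, since 0.7 × 0.7 = 0.49 of the shift is recovered.

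**Set against the noise.** The residual SD is √(1 − 0.5²) = 0.866. With 54 and 46 attenders the standard error is 0.866 × √(1/54 + 1/46) = 0.17; with 45 and 30 it is 0.20. A gap of 0.06 to 0.12 SD is below one standard error and could easily be read as agreement.

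**On the value 0.40.** It is the article's stated detectable effect, used here for illustration. It is not reproduced by an unadjusted two-sided two-sample calculation with 50 per arm: (1.960 + 0.842) × √(2/50) = 0.56. That is a separate matter. The true effect does not enter the bias term.

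**The case against.** The strongest reply is that delta-adjusted analyses usually live in a statistical analysis plan, which is not at hand, and that the article says nothing false. It calls the comparison supplementary and never offers it as proof of robustness. This stands in part: the absence of a tipping-point analysis is not a finding in itself. What remains is that the check the article does fix is largely uninformative about the main missing-data risk.

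Four stronger readings are tempting and not supported:
- *The comparison will always look reassuring.* The imputation model is unstated. If it includes on-treatment craving and use, imputation rests on a weaker assumption than the attenders-only model, and the comparison carries some information.
- *The primary aim itself predicts unequal study dropout.* It predicts better treatment retention. Someone can stop treatment and still attend week 10, and the article plans repeated contacts to keep participants in the study. The Introduction's six-month figures are background on buprenorphine treatment, not on missed visits in this trial.
- *Imputation is certain to become the primary method.* The 16.7% is an allowance for completion at an unspecified point. Visits run to week 20, so week-10 loss may be smaller.
- *The bias must favour one arm.* It depends on which arm loses more participants with poor outcomes.

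It can also be said that the article names 100 people, the completion number, as its target, so that an effect in everyone randomised is not its stated aim. But imputing the missing outcomes makes sense only if participants beyond the attenders matter.

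**Conclusion.** The point holds in a limited form. Agreement between results with and without imputation is weak evidence against informative dropout: close to none if imputation uses only the analysis-model variables, and limited if on-treatment measures are added.

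The effect is understated if sham loses more participants with poor outcomes, overstated if active does, and nearly unbiased if loss and shift are equal across arms. With a 10%/23.3% split and shifts of 0.4 to 0.8 SD the bias is about 0.05 to 0.11 SD, and about half that with 13.3%/20%. This is modest and below one standard error. It rests on assumed splits, shifts and correlations, and on simulations of a continuous craving score. Days of use was not simulated, though the same reasoning applies. The documents do not show that such dropout will occur. They show that it is plausible and that the stated check would be poor at revealing it. This is a cheap improvement, not a fault that invalidates the primary analysis.

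**What to change.** In the section on data retention and missing data, keep the comparison with and without imputation as a descriptive result. Add a pre-specified delta-adjusted version of the planned imputation for week-10 craving and days of use:
- Shift the imputed values towards worse outcomes over a fixed grid, for example 0 to 0.8 SD for craving and 0 to 7 days for use, with imputed days kept within 0 to 7.
- Vary the shift separately by arm, so that unequal shifts in either direction are covered.
- Report the shift at which the conclusion changes, and base any statement about robustness to missing data on this analysis.

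The cost is a sentence or two of text and a few more runs of the 100 imputed datasets already planned, with no extra participants or visits. The downside is that the result may look less robust than under the present comparison. Recruitment is under way, so the grid is most credible if fixed before outcomes by arm are seen.

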## Discussion

We describe a protocol for a multisite trial of TMS for OUD for individuals taking buprenorphine using a novel treatment schedule that optimizes for feasibility and efficiency. This protocol will evaluate the effectiveness of a therapeutic TMS intervention for reducing craving and opioid use in individuals receiving treatment for OUD. This protocol will extend prior work by administering TMS on a novel weekly schedule that more closely reflects typical clinical practice, and will focus on participants maintained on buprenorphine, the most commonly prescribed medication for OUD. In addition, the protocol will include neuroimaging to assess changes in neural circuitry associated with TMS intervention, which may help clarify potential mechanisms underlying treatment effects.

A key strength of this protocol is its focus on improving feasibility and generalizability of TMS for OUD – directly addressing limitations of prior clinical protocols. For example, a study conducted in China demonstrated TMS-related reductions in craving among individuals with OUD [33]; however, participants were inpatients, were not receiving pharmacological treatment, and were exclusively using heroin. These conditions differ substantially from those in the United States, where most individuals receiving treatment for OUD receive outpatient treatment with medications such as buprenorphine and are required to attend regular clinic visits. In contrast, the only study to implement a therapeutic TMS protocol in North America reported significant challenges with recruitment and retention, requiring participants to attend sessions five days per week for four weeks [26]. As noted by the authors, low retention likely reflects the complex nature of OUD, in which a range of social, medical, and personal factors can affect treatment engagement [26,34], and more broadly suggests that intensive daily TMS schedules may not be feasible in this population. These observations thus highlight the need to develop protocols that are better aligned with patient needs and real-world care contexts [35]. Indeed, prior work suggests that the spacing of TMS treatments (e.g., daily vs weekly) is less critical than the total number of treatments or pulses delivered for providing therapeutic benefit [36,37]. Notably, participants enrolled in this protocol will receive a higher dose of TMS (i.e., more pulses) than the FDA-approved standard iTBS protocol (in which iTBS is delivered daily) while simultaneously fitting the treatment course into the cadence of weekly clinical visits for buprenorphine prescriptions. Additionally, while accelerated TMS protocols have shown promise in treating psychiatric conditions [29,30], the effect of spacing treatment is still untested. Thus, our approach of aligning TMS sessions with routine clinical visits may reduce participant burden without compromising dosage and may ultimately improve treatment adherence.

An additional strength of this protocol is the inclusion of a non-academic clinical site for data collection, which may enhance generalizability to real-world settings. Much of the existing TMS research has been conducted in academic medical centers. While these settings provide important infrastructure, they may not reflect the environments in which most patients receive care. As TMS becomes more widely available in private psychiatric clinics, evaluating protocols in these settings is increasingly important. By including a study site at a private psychiatric clinic, this protocol extends assessment to a more representative care setting, which may further enhance the feasibility and clinical applicability of the protocol beyond its clinical benefits.

Reducing craving, and in turn opioid use, is the primary clinical target of this protocol. Craving is a central feature of OUD [38] and is the strongest predictor of drug use and relapse for people with SUD [39–41]. Craving is described as the subjective experience of wanting to use a drug [42] and exposure to cues that induce craving can more than triple the odds of drug use [39]. Importantly, treatment with buprenorphine only partially attenuates craving, which can lead to a return to opioid use [2]. Consistent with this, previous work has directly linked craving to subsequent opioid use after buprenorphine treatment initiation [43]. Given the ubiquity of patient reports of craving and its hinderance to recovery, there has thus been a push to directly address craving in the treatment of OUD [38,44]. Accordingly, the current TMS protocol may represent a complementary intervention to target this key driver of continued use and return to use, with the potential to improve clinical outcomes.

While improving outcomes is the first step toward implementing TMS in OUD populations, it is equally critical to understand the mechanisms underlying its therapeutic effects [45]. To address this, we will incorporate neuroimaging to assess changes in neural circuitry associated with TMS intervention. Substantial evidence indicates that individuals with substance use disorders exhibit dysfunction in fronto-striatal circuits that increase drive for drug-seeking and reduce behavioral control [46–48]. Specifically, dysfunctional connectivity between the striatum and DLPFC is associated with increased drug use and impulsivity, dependence severity and increased cue-induced craving [49–53]. Importantly, a key mechanism by which TMS is thought to exert its therapeutic effects is via dopaminergic modulation of the striatum through stimulation of the DLPFC [54]. Work has demonstrated that DLPFC stimulation promotes dopamine release in the striatum [55,56] which may then counteract dopamine hypoactivity that is common in substance use disorders [57,58]. Together, these findings suggest that targeting DLPFC-striatal connectivity may serve as an effective intervention to reduce craving and return to use in individuals with OUD and highlight the importance of using neuroimaging to evaluate whether this TMS intervention engages these circuits and leads to clinically meaningful changes in craving.

While this study has several strengths, some limitations of the protocol highlight important unanswered questions in the field that we can start to address. First, the inclusion criteria may result in a relatively restricted sample, as participants are required to have no concurrent SUD (other than nicotine or cannabis) and no major co-occurring psychiatric disorders. Concurrent substance use is common in people with OUD, with estimates suggesting that more than 25% of individuals have a co-occurring alcohol and/or stimulant use disorder [59,60]. These SUDs present concerns regarding safety as well as scientific validity, necessitating limiting their occurrence in this protocol. Similarly, co-occurring psychiatric disorders, such as depression, anxiety and post-traumatic stress disorder (PTSD), are highly prevalent [61,62]. However, it remains an open question whether TMS protocols targeting OUD-related outcomes may convey broader therapeutic benefits. Notably, given that TMS is already cleared for depression [10] and has demonstrated efficacy in PTSD [63], this study will also collect data on these symptoms to help clarify potential secondary therapeutic benefits. Importantly, recruitment through outpatient clinics that provide buprenorphine treatment will allow for direct collaboration with clinicians to identify appropriate candidates, and inclusion of two study sites will help to broaden the available sample of participants. Second, we will use a novel dosing schedule, with twice-weekly TMS sessions delivered on a single day. While this approach may improve feasibility, the existing literature supports treatment efficacy based on the number of sessions, rather than pulse count alone [64–67]. As such, the proposed schedule should be considered exploratory, and its effects in this population remain to be established. Third, the optional neuroimaging component raises additional questions about the feasibility of integrating neural biomarkers into clinical protocols of TMS for OUD. While optional participation in this component may reduce participation in this aspect of the study and limit the completeness of mechanistic analyses, the close proximity of neuroimaging facilities may reduce participant burden and facilitate greater participation in imaging procedures.

## Conclusion

If successful, this study will identify a safe and potentially effective adjunctive intervention for reducing craving and return to use in individuals with OUD that is feasible and ready to be implemented in TMS clinics. It will also provide insight into the neural mechanisms underlying changes in craving associated with TMS treatment. By targeting craving – a key contributor to continued opioid use – this approach may help improve clinical outcomes and address limitations of existing treatments for a condition associated with substantial morbidity and mortality.

Figures were created in https://BioRender.com
